## Study Identification

Unique Protocol ID: CSU-2017-001

Brief Title: A Good Start to Life - an Early Cross-sectorial Intervention

Official Title: Early Prevention of Social Inequality in Health - an Interdisciplinary and Cross-sectorial Intervention for Vulnerable Pregnant Women

Secondary IDs:

## Study Status

Record Verification: June 2017

Overall Status: Enrolling by invitation

Study Start: June 16, 2017 [Actual]

Primary Completion: June 30, 2019 [Anticipated]

Study Completion: June 30, 2019 [Anticipated]

## Sponsor/Collaborators

Sponsor: Intersectoral Research Unit for Health Services

Responsible Party: Sponsor

Collaborators: University of Copenhagen

## Oversight

U.S. FDA-regulated Drug: No

U.S. FDA-regulated Device: No

U.S. FDA IND/IDE: No

Human Subjects Review: Board Status: Approved

Approval Number: 17006186

Board Name: The Regional Committee on Health Research Ethics

Board Affiliation: The Danish Capital Region

[contact]

Email: [contact]

Address:

[name]

[name]

Denmark

Data Monitoring: Yes

## Study Description

**Brief Summary:** The aim of the project is to develop and evaluate an interdisciplinary and cross-sectorial intervention targeting pregnant women with psychosocial vulnerabilities. The objective is to 1) detect depression, anxiety and personality disorders in the pregnant women, 2) to increase knowledge sharing across the health care sectors and 3) strengthen the parents' parenting skills and thereby support a secure attachment between parents and child and thus promoting the child's well-being.

The overriding hypothesis is that an early multi-stringed, interdisciplinary and cross-sectorial intervention, with a long-term perspective from the early pregnancy throughout the child's first years of life, can effectively prevent disorders in the parent-child relation. The approach is to detect and treat depression and anxiety in the mother and strengthen the parents' parenting skills in families with maternal psychosocial vulnerabilities. The hypothesis indicates that the over-all intervention will result in improved interaction between child and parents which will make it possible to detect higher maternal sensitivity and a higher level of well-being among both children and parents in the intervention group compared to the control group.

The projects' specific hypotheses are;

- A systematic screening for anxiety, depression and personality disorders in the midwifery consultation will imply more pregnant women with symptoms of anxiety, depression and personality disorders being detected and offered treatment in the intervention group compared to the control group.
- Knowledge sharing across health care sectors will improve by the implementation of a joint consultation involving the vulnerable pregnant woman/families, the midwife and the health visitor and by a systematic transmission of information when the woman leaves the post-natal ward and is transferred to the health visitor.
- Parental skills in psychosocial vulnerable pregnant women and their partners can be strengthened by a parental training program and by education and dialogue about perceived challenges and breast-feeding. Parents in the intervention group will therefore gain greater knowledge on what it takes to make breast-feeding work successfully, be able to interact more appropriate with their children, and improve their mentalization skills and experience less stress compared to parents in the control group.

**Detailed Description:** Design, material and method:

The project will be conducted as a randomized controlled trial. The intervention group will receive a specific intervention and the control group will receive care as usual, in this context the standard treatment in antenatal care for vulnerable pregnant women and by the health visitor.

**Study setting:**

The intervention will be executed on Herlev-Gentofte Hospital in Denmark and in four of the affiliated municipalities: Ballerup, Gentofte, Herlev and Rødovre.

**Target group:**

The intervention is targeted vulnerable pregnant women who do not have psychiatric diagnosis or problems related to drug abuse, are not treated at family outpatient clinic or comprehensive municipal precautionary interventions (care level 4\*), but who has the need for more than the standard treatment due

to psychological and/or social challenges (e.g. previous traumas, problematic family relations or acute life crisis). Hence, the target group of the study is women with psychological or social vulnerabilities and classified as care level 3 by the hospital.

It is estimated that the project can identify 100 pregnant women from the target group from the four municipalities during the inclusion period of 10 months. An expected drop-out on 20 % will result in an expected amount of 80 pregnant women who can complete the project.

#### Recruitment:

Participants are recruited among pregnant women who are referred to give birth at Herlev-Gentofte Hospital. On the basis of information from the general practitioner, the referring midwife refers the pregnant women to one out of four care levels. From the above mentioned inclusion and exclusion criteria the pregnant women from care level 3\* is identified as being in the target group by the referring midwife. Afterwards, the women are recruited to the project through an enclosed invitation and information leaflet, send from the hospital together with a notice for the first midwife consultation. Next, project personnel contact the pregnant women to consult whether they are interested to participate in the research project. Then, the project personnel visit the potential participants in their homes to give further information on the project and include the interested women and their families in the project.

#### Selection of intervention hospitals and municipalities:

An examination of existing or previously interventions targeting vulnerable pregnant women in the Capital Region of Denmark was utilized in the process of selecting hospitals and municipalities in the intervention and control group. Herlev-Gentofte Hospital was invited to participate in the project as these hospitals were suitable with regard to the projects key intervention components and already existing interventions on the hospitals and affiliated municipalities. The included municipalities confirmed that they are not participating in other research project in the field of early prevention of social inequality in health among vulnerable pregnant women as long as this project last. The municipalities are: Herlev, Ballerup, Rødovre and Gentofte.

#### Data collection:

Data for evaluating the efficiency of the intervention are collected on three points of time; at baseline, after birth, when the child is aged four weeks, and at follow-up after the intervention has finished, when the child is around nine months. All data are collected in the homes of the families. To make an extra incentive to complete the questionnaires the participants receive a gift to the value of approx. 300 dk. kr. (approx. 45 USD) when completion of the follow-up questionnaire. Baseline data is collected for both control and intervention group before participants are familiar with the allocation of the randomization. The following paragraphs will describe the type of data that will be collected. Table 4 shows an overview of variables expected to be collected. Two different questionnaires will be developed specifically for the mother and for the father. The questionnaires look alike except that the mother's questionnaire contains questions on her attachment to the child in the belly and on her attitude and perception of breast feeding.

The questionnaires will be pilot tested by individuals from the target group to ensure that the questionnaires have a manageable size for participants and that questions are relevant. Afterwards the questionnaire will be revised accordingly.

#### Planned statistical methods:

The analyses will be performed using the statistical software Statistical Analysis System (SAS) 9.4. Analysis and presentation of data will be in accordance

with the CONSORT guidelines (reference). Standard descriptive statistics (means, medians, ranges, standard deviations, frequencies and percentages) will be used to report demographics, baseline and outcome scores. Data will be examined for missing data and multiple imputation strategies will be used if necessary. It is expected that the frequency of missing data will be low as data are collected through home interviews.

The analysis of both primary and secondary endpoints will follow the intention-to-treat principles. However, analyses taking the actual treatment participation into account will also be conducted. To examine how non-compliance affects the results different levels of participation will be investigated.

Primary and secondary outcomes will be analyzed using multiple regression for continuous outcomes, and logistics regression for binary outcomes controlling for baseline scores when possible.

\* \* The Danish Health Authority's recommendations for antenatal care prescribe the general practice to classify all pregnant women in care level 1-4 based on a psychosocial anamnesis. Pregnant classified in care level 1 receives the standard intervention; pregnant in level 2 receives an extended intervention in the context on antenatal care based on e.g. previously birth complications or disease; pregnant in level 3 receives an extended intervention including involvement of other professional groups in the health care sector or municipality based on complex social, medical or psychological problems; and pregnant in level 4 receives an extensive interdisciplinary and intersectorial intervention, including collaboration with specialized institutions based on highly complex problems e.g. alcohol or drug abuse, severe mental/psychiatric diseases and/or severe social load

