## Study Design

Study Type: Interventional

Primary Purpose: Prevention

Study Phase: N/A

Interventional Study Model: Parallel Assignment

The study population will be stratified randomized on an individual level, thus half of the women, who agree to participate, is being randomized to the intervention group and the other half is being randomized to the control group. The trial participants will be allocated within each municipality to either control- or intervention group. The project personnel visiting the families to collect baseline data carry out the randomization. The project personnel bring a sealed envelope when visiting the families. In the envelope, the randomization group is stated together with a randomization number. The envelope is packed by a third party individual who receives a computer generated allocation list from another researcher. The envelopes get the numbers from this random sequence. The researcher generates the allocation list by block randomization with random

block sizes of 2. The random allocation list is generated once and will be destroyed after the sealed envelopes are packed.

Number of Arms: 2

Masking: Investigator, Outcomes Assessor

Allocation: Randomized

Enrollment: 100 [Anticipated]

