## Outcome Measures

### Primary Outcome Measure:

#### 1. Maternal sensitivity

Sensitive responses, that is the ability to respond appropriately to the child's attachment needs, has consistently been found to be the most reliable predictor of attachment security. The intervention, including The Circle of Security, has the aim to promote maternal sensitivity.

The measurement tool "Coding Interactive Behaviour" (CIB) will be used to code maternal sensitivity towards the child. Maternal sensitivity is observed during 5 minutes interaction (free play) between mother and infant.

CIB has good psychometric properties and has been validated in multiple longitudinal studies across cultures and across age groups (from newborn to adolescent). The system has previously been used for the purpose of research of the relation between a child and a mother with mental illness(es). Moreover, it has been used to evaluate the effectiveness of interventions.

[Time Frame: The mother-child relation will be videotaped and assessed during a home-visit by the health visitor after the intervention is finished when the child is around 9 months old.]

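### Randomization is stratified by municipality, but the stated model does not name municipality, and its baseline-score rule gives the primary outcome no adjustment on a plain reading

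*Protocol*

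**What the plan says.** **Randomization (Protocol, Study Design).** "The study population will be stratified randomized on an individual level", and "The trial participants will be allocated within each municipality to either control- or intervention group". Allocation is 1:1 with "block sizes of 2". The Study setting section gives the strata: "four of the affiliated municipalities: Ballerup, Gentofte, Herlev and Rødovre".

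**Analysis (Protocol, Planned statistical methods).** One covariate rule covers all primary and secondary endpoints: "multiple regression for continuous outcomes, and logistics regression for binary outcomes controlling for baseline scores when possible". Municipality does not appear in it, no other covariate is listed, and the section does not say which baseline scores are meant.

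**Primary outcome (Protocol, Outcome Measures, item 1).** Maternal sensitivity is coded with CIB from five minutes of free play between mother and infant, "after the intervention is finished when the child is around 9 months old". The only other CIB measurement is item 18, a secondary outcome taken when the child is about 1 month old.

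**Sample size (Protocol, Target group).** 100 women enrolled, 20% drop-out expected, 80 completers. No alpha, power, effect size or standard deviation is given.

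**The concern.** Two features of the design do not meet in the stated model.

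First, blocking within municipality forces the arms to be balanced on municipality. If mean outcome differs between municipalities, that balance makes the treatment estimate more precise. A model without municipality leaves the between-municipality variation in its residual, so it reports a standard error larger than the true one. The interval is then wider than the design warrants.

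Second, the adjustment rule refers to baseline scores, and the primary outcome has none of its own because there is no infant to observe at baseline. Read plainly, the rule works for outcomes such as the EPDS, which is measured at baseline and at both follow-ups, and does nothing for the one outcome on which the trial is judged. Yet other maternal scores are collected at baseline: EPDS, antenatal attachment, prenatal reflective functioning, mental well-being and adult attachment.

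At stake is precision in a trial of about 80 completers, and a primary model whose covariates are settled in advance.

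**Working it through.** **Step 1: the Protocol's own figure.** 100 × (1 − 0.20) = 80, which reproduces. With 1:1 allocation this is about 40 per arm. There is no power statement to reproduce.

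**Step 2: assumptions not in the documents.** Two-sided alpha 0.05, outcome SD 1, and a share R² of outcome variance lying between municipalities, varied from 0 to 0.20. The effect used is about the difference detectable with 80% power at 40 per arm: (1.960 + 0.842) × √(2/40) = 2.802 × 0.2236 = 0.63 SD.

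**Step 3: expected standard errors.**
- Treatment-only model: √(2/40) = 0.224, whatever R² is.
- With municipality: √((1 − R²) × 2/40), ignoring small losses from imbalance after drop-out. R² = 0.05 gives 0.218, R² = 0.10 gives 0.212, and R² = 0.20 gives 0.200.

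**Step 4: simulation with drop-out.** 100 women in four strata of 24 to 26, blocks of two within stratum, and 80 retained at random. Ordinary least squares with arm only was compared with arm plus municipality. There were 6,000 trials under no effect and 3,000 at 0.63 SD.

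| Municipality share R² | Type I error, arm only | Type I error, with municipality | Power, arm only | Power, with municipality | Power difference (points) |
|---|---|---|---|---|---|
| 0 | 0.052 | 0.053 | 0.785 | 0.781 | −0.4 |
| 0.02 | 0.047 | 0.049 | 0.802 | 0.801 | 0.0 |
| 0.05 | 0.046 | 0.050 | 0.802 | 0.809 | 0.7 |
| 0.10 | 0.042 | 0.052 | 0.800 | 0.824 | 2.4 |
| 0.20 | 0.031 | 0.050 | 0.811 | 0.873 | 6.2 |

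Monte Carlo standard errors are √(0.05 × 0.95/6000) = 0.003 for type I error and √(0.8 × 0.2/3000) = 0.007 for power.

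Under no effect, the arm-only model's average reported standard error can be set against the actual spread of its estimates. At R² = 0.10 these are 0.2233 and 0.2154, a ratio of 1.04. At R² = 0.20 they are 0.2237 and 0.2042, a ratio of 1.10. With municipality in the model, the average reported standard error falls to 0.2125 and 0.2004, close to Step 3.

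**Step 5: a second simulation.** Four strata of 20, no drop-out, 4,000 trials per scenario, and municipality shares of 5, 10 and 15%. Arm-only type I error was 0.044, 0.041 and 0.033. Power rose from about 0.80–0.81 to 0.82, 0.84 and 0.84 with municipality. At a 5% share this is a gain of 1 to 2 points, against 0.7 in Step 4, hence the stated range of about 0 to 2 points at 5% or less.

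**Step 6: adding a baseline score.** In the same simulation, a covariate assumed to explain a further 10, 15 or 20% of variance brought power to 0.85, 0.90 and 0.92. The corresponding standard errors were 0.207, 0.194 and 0.181. The covariate shares are hypothetical.

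**Step 7: degrees of freedom at 80 completers.** Arm only: 80 − 2 = 78. With municipality: 80 − 5 = 75. With two baseline scores as well: 80 − 7 = 73.

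All figures are for a continuous outcome. None was computed for the logistic models.

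**The case against.** The strongest reply is that silence is not exclusion. The methods sentence does not say that baseline scores are the sole covariates, and multiple regression suggests that there may be others. A full covariate list, stratification factors included, is commonly left to the SAP, which was not available here. This stands in part. It would be wrong to say that the plan rejects municipality; it does not name it. But the Protocol does state an adjustment rule for the primary and secondary outcomes, and that rule, followed as written, contains no stratum term.

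Second, a reader might infer that the primary analysis is certainly unadjusted. The text does not establish that. Baseline scores could mean any score taken at baseline, and several maternal scores are available. That reading is open, but the Protocol does not choose it or say which scores would enter.

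Third, a reader might fear that the 1-month CIB score would serve as the baseline. The documents do not support this. The Data collection section separates baseline from the four-week visit, and item 18 lists the 1-month score as a secondary outcome.

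Fourth, the size is modest and rests on assumed variance shares. Nothing in the Protocol shows how much CIB scores differ between four municipalities that share one hospital and one care level. No correlation between any baseline score and CIB is given either. This stands in full, so the power figures of 0.85 to 0.92 cannot be offered as an expected gain.

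**Conclusion.** The point holds as one about precision and clarity. The stated model does not name the factor used to stratify randomization. Its adjustment rule, read plainly, does nothing for the primary outcome.

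A reader might infer that the primary test is invalid, but it is not. With 1:1 allocation inside every municipality, the arm-only estimate is unbiased. The simulated type I error without municipality stays at about 0.05 or below; the test becomes conservative as municipalities differ more.

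If municipality explains 0 to 20% of variance, type I error goes from about 0.05 to about 0.03, and about 0 to 6 points of power are lost at 0.63 SD. At a share of 5% or less, the loss is about 0 to 2 points. These figures assume 80 completers, drop-out at random where it was modelled, two-sided alpha 0.05 and a continuous outcome. The further gain from baseline scores may be larger or negligible; the documents give no basis for estimating it.

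**What to change.** In the Planned statistical methods section, replace the open-ended qualifier with a fixed rule:

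- Models for all outcomes measured after randomization include arm and municipality (four levels). Items 2, 6 and 12 are listed at baseline only, so they have no treatment effect to model and fall outside this rule.
- The primary CIB model also adjusts for one or two baseline scores already collected, named before unmasking. EPDS and antenatal attachment are examples; naming them in advance matters more than which are chosen.
- The 1-month CIB score remains a secondary outcome, as already listed, and is not a covariate for the 9-month comparison. It is measured after randomization and after the intervention's prenatal visits.

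The cost is a few sentences and three to five degrees of freedom out of about 78. If municipality explains nothing, the simulated power cost of including it is about 0.4 points. No new data are needed, and the Protocol's record shows the trial still enrolling.

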## Conditions

Conditions: Anxiety  
Attachment Disorder  
Maternal Sensitivity  
Depression  
Personality Disorders

Keywords:

## Study Design

Study Type: Interventional

Primary Purpose: Prevention

Study Phase: N/A

Interventional Study Model: Parallel Assignment

The study population will be stratified randomized on an individual level, thus half of the women, who agree to participate, is being randomized to the intervention group and the other half is being randomized to the control group. The trial participants will be allocated within each municipality to either control- or intervention group. The project personnel visiting the families to collect baseline data carry out the randomization. The project personnel bring a sealed envelope when visiting the families. In the envelope, the randomization group is stated together with a randomization number. The envelope is packed by a third party individual who receives a computer generated allocation list from another researcher. The envelopes get the numbers from this random sequence. The researcher generates the allocation list by block randomization with random

block sizes of 2. The random allocation list is generated once and will be destroyed after the sealed envelopes are packed.

Number of Arms: 2

Masking: Investigator, Outcomes Assessor

Allocation: Randomized

Enrollment: 100 [Anticipated]

## Arms and Interventions

| Arms                                                                                                                                                                                                                                                                                                                                                                                                                                                                                                | Assigned Interventions                                                                                                                                                                                                                                                                                                                                                                                                                                                                                                                                                                                                                                                                                                                                                                                                             |
|-----------------------------------------------------------------------------------------------------------------------------------------------------------------------------------------------------------------------------------------------------------------------------------------------------------------------------------------------------------------------------------------------------------------------------------------------------------------------------------------------------|------------------------------------------------------------------------------------------------------------------------------------------------------------------------------------------------------------------------------------------------------------------------------------------------------------------------------------------------------------------------------------------------------------------------------------------------------------------------------------------------------------------------------------------------------------------------------------------------------------------------------------------------------------------------------------------------------------------------------------------------------------------------------------------------------------------------------------|
| Experimental: Intervention
The intervention consists of three key components aiming at promoting a better attachment between child and mother/parents and through that giving the child the best possible beginning of life. The three components aim at: 1) detecting ill-being in vulnerable pregnant woman and initiation of potential treatment, 2) strengthening knowledge sharing and organizing the course for the families across the sectors, 3) strengthening parenting skills. | Behavioral: Intervention
1) Detection of ill-being: An extended consultation with the midwife. The midwife will screen the women for symptoms of anxiety, depression and personality disorders. 2) Knowledge sharing: An additional midwife consultation accompanied by the health visitor. The aim of is sharing knowledge and transmission of information between the two sectors responsible for making a shared plan for the course of the process for the pregnant woman. 3) Strengthen parenting skills through: - Two visits by the health visitor before birth and eight after. The visits are based on the parent training program The Circle of Security, aiming at promoting a secure attachment between child and carer. - Teaching the woman/couple on the importance of breast-feeding and how to succeed. |
| No Intervention: Control
The existing practice for psychosocial vulnerable pregnant women on Gentofte-Herlev Hospital, Denmark, will be offered for women allocated to the control group. The control group will be measured at the same follow-up periods as the intervention group.                                                                                                                                                                                                     |                                                                                                                                                                                                                                                                                                                                                                                                                                                                                                                                                                                                                                                                                                                                                                                                                                    |

